## Abstract

**Background::**

Functional dyspepsia (FD) is a highly prevalent functional gastrointestinal disorder which brings a significant impact on patients’ quality of life. Although there are many available treatments to alleviate dyspepsia symptoms, most of them are far from satisfactory. Traditional Chinese medicine (TCM) has shown good potential in the treatment of FD, especially in terms of improving symptoms and adverse effects of Western medicine. Qizhi Weitong granule (QZWTG), a TCM preparation, has been utilized in treating FD for a long time and has achieved good clinical results. However, the existing evidence of its efficacy and mechanism of action is insufficient. Hence, the purpose of this study is to evaluate the efficacy and safety of QZWTG in the treatment of FD.

**Methods::**

This study is a multicenter, randomized, double-blinded, double-placebo, positive drug parallel controlled clinical study. The experiment will be carried out in 8 hospitals at the same time, and a total of 384 cases of participants will be randomly assigned to the experimental group and the control group (n = 192). The experimental group will be given QZWTG and Mosapride citrate tablet placebo, and the control group will be given QZWTG placebo and Mosapride citrate tablet. After 4 weeks of intervention and 2 weeks of follow-up, the efficacy and safety of QZWTG in patients with FD will be observed. The primary outcomes are the change in the main symptom score. The secondary outcomes include TCM syndrome evaluation, the change of the Hamilton anxiety scale and the Hamilton depression scale, and advanced events. This study will explore the biological mechanism of QZWTG in the treatment of FD through the results of blood and urine metabolomics.

**Discussion::**

This trial will provide first-hand evidence on whether QZWTG is noninferior to Mosapride citrate tablet. There will be a new option for the treatment of FD if noninferiority is set up. In addition, the efficacy and safety of QZWTG in the treatment of FD will be evaluated, and the mechanism of QZWTG in the treatment of FD will be explored through the metabolomics of blood and urine. On the other hand, as far as we know, this study may be the largest trial of efficacy and safety of QZWTG in the treatment of FD, which has important application value.

## Introduction

1

Functional dyspepsia (FD) is one of the most common functional gastrointestinal disorders,^[1]^ which is characterized by a series of dyspepsia symptoms such as postprandial fullness, early satiation, epigastric pain, in the absence of structural explanation.^[2]^ The overall global prevalence of dyspepsia has been estimated to be 20% to 40%.^[3]^ In Rome IV, according to the difference of main symptoms, FD can be divided into 2 subgroups: postprandial distress syndrome (PDS) and epigastric pain syndrome (EPS), also, the 2 subgroups can overlap.^[2]^ A recent study shows that approximately 10% of the adult population from the USA, Canada, and the UK fulfills symptom-based criteria for Rome IV criteria of FD.^[4]^ Although FD is not life-threatening, it brings a significant impact on patients’ quality of life.^[5]^

At present, FD is considered to be caused by multiple factors, which may be related to abnormalities of gastric motility, gastric hypersensitivity, brain-gut interaction,^[6]^ duodenal acid,^[7]^ duodenal bile, duodenal barrier defect, and immune activation.^[8]^ Gastric motility disorder and sensorimotor abnormality are recognized as one of the main factors leading to FD, and prokinetics are recommended for the treatment of FD.^[2,9]^ Although, a number of randomized controlled clinical studies have shown that the efficacy of prokinetic agents,^[10–12]^ such as Cisapride, in patients with FD is significantly higher than that of placebo, which can significantly alleviate the symptoms of dyspepsia,^[13]^ such as upper abdominal fullness,^[14]^ but the clinical application of it is limited due to the side effects of heart.^[15]^ In addition, existed treatment options may be effective for FD, but their therapeutic effect is far from satisfactory. Due to the high prevalence of FD and the lack of effective treatments, FD is now a considerable clinical problem for the healthcare system.^[16]^

Traditional Chinese medicine (TCM) has shown good potential in the prevention and treatment of FD, especially in terms of relieving symptoms and adverse effects of Western medicine.^[17,18]^ Therefore, it is necessary to seek a supplementary therapeutic approach for the treatment of FD.

QZWTG is a TCM preparation and is commercially developed to relieve epigastric distress and pain. QZWTG is composed of 6 kinds of Chinese herbals (Table 1): Radix Bupleuri (Chaihu), Rhizoma Corydalis (Yanhusuo (baked)), Fructus Aurantii (Zhike), Nutgrass Galingale Rhizome (Xiangfu (baked)), Radix Paeoniae Alba (Baishao), and Radix Glycyrrhizae Preparata (Zhigancao). All herbs were tested to the same standard. QZWTG is developed by the China Resources Sanjiu Pharmaceutical Co., Ltd: [name] and is approved for production on the market. The drug approval No.: gyzz21021522. At present, QZWTG has been approved by the State Food and Drug Administration for clinical treatment in Gastrointestinal motility and sensory disorders related diseases,^[19,20]^ and have achieved good results. QZWTG has the functions of soothing the liver, regulating qi, relieving pain in the stomach, and used to relieve symptoms such as epigastric dull pain, fullness, acid regurgitation, nausea, vomiting, reduction of appetite, and noise in heart and mouth. Previous research^[21]^ has shown that QZWTG has a significant symptomatic improvement over placebo in patients with PDS. Moreover, QZWTG has been proved that it has the effect of improving gastric motility,^[22–26]^ and has no side effects such as the central nervous system and cardiovascular system.^[21]^ However, the consistency of this effect remains uncertain. In addition, there is a lack of comparative studies between QZWTG and existing treatment methods, such as Mosapride, a prokinetic agent.

**Table 1 T1:**
[figure not shown]
Main components of Qizhi Weitong granules.

The aim of this randomized, double-blinded, double-placebo, positive drug parallel controlled, multicenter clinical trial was to further verify the therapeutic effect of QZWTG compared with Mosapride in patients with FD, and observe the effectiveness and safety of QZWTG on different subtypes of FD, so as to guide clinical practice.

## Methods

2

### Study design

2.1

This trial is a multicenter, randomized, double-blinded, double-placebo, positive drug parallel controlled clinical trial. A total of 384 patients will be enrolled and randomly assigned to 1 of 2 groups: Qizhi Weitong and Mosapride group. After 1 week of the screening period, 4 weeks of intervention, and 2 weeks of follow-up, the effectiveness, and safety of QZWTG will be evaluated by comparing the various indicators of the 2 groups, including clinical symptoms, biochemical indicators. This study will be conducted with the principles of the Declaration of Helsinki and Good Clinical Practice guidelines, and the Consolidated Standards of Reporting Trials 2017 for Chinese herbal medicine (CHM) recommendations.^[27]^

As the leading unit of the research, Xiyuan hospital is responsible for training the standard operating procedures (SOPs) of researchers and supervising the progress of all clinical sites. Other participating units include the Beijing Friendship Hospital Affiliated to Capital Medical University, the First Affiliated Hospital of Guangzhou University of Traditional Chinese Medicine, the First Affiliated Hospital of Zhejiang University, Shengjing Hospital Affiliated to China Medical University, the First Affiliated Hospital of Henan University of Traditional Chinese Medicine, Jiangsu People's Hospital, Zhongshan Hospital affiliated to Fudan University. Recruitment allocation: 384 cases will be competition among centers. The Consolidated Standards of Reporting Trials flow diagram of this trial is briefly illustrated in Figure 1. This study protocol is registered with the ClinicalTrials (NCT03149393).

**Figure 1 F1:**
[figure not shown]
CONSORT flow diagram for QZWTG. CONSORT = clinical practice guidelines, and the consolidated standards of reporting trials, QZWTG = Qizhi Weitong granule.

### Participant recruitment

2.2

Inpatients and outpatients with FD from the 8 participating hospitals will be enrolled. Two experienced gastroenterologists will screen the patients according to the inclusion and exclusion separately. Patients assessed by 2 doctors meeting the criteria of the trial will be included in the trial. In addition, the recruitment advertisements for this trial will be in the form of posters and webpages in the 8 research units for public recruitment. It mainly includes a brief introduction of the drugs, treatment methods, and the rights and interests of the patients in this study. For those who refuse to participate, we will record their basic information and the reasons for refusing to participate. The trial started in January 2017 and will end in December 2020.

### Diagnostic criteria

2.3

#### Diagnostic criteria of FD

2.3.1

The diagnostic of FD will refer to the criteria published in Rome IV^[2]^:

(1)One or more of the following: A. The discomfort of fullness after a meal; B. early satiety; C. upper abdominal pain; D. upper abdominal burning.(2)There is no evidence of structural disease that can explain the above symptoms, and no organic disease is found by gastroscopy or barium contrast examination of the upper gastrointestinal tract, and the examination time is after the occurrence of symptoms;(3)The symptoms appeared at least 6 months before diagnosis, nearly 3 months met the above diagnostic criteria.

#### Inclusion criteria

2.3.2

Patients must meet both of the inclusion criteria of the screening period and treatment period.

Screening period criteria:

(1)Meeting the diagnostic criteria of FD in Rome IV;(2)Age 18 to 65 years old, gender is not limited;(3)The subjects were informed, and the subjects voluntarily signed informed consent;(4)The subjects have the reading ability.

Treatment period criteria:

(1)Patients continued to be willing to participate in the study;(2)After treatment in the screening period, the sum of at least 1 symptom score (degree + frequency) is still ≥4 points, and the reduction rate is ≤50%.

#### Exclusion criteria

2.3.3

Patients who meet 1 or more of the exclusion criteria listed below will not be allowed:

(1)Patients suffering from gastric ulcer, gastroscopy see bleeding and mucosal erosion, pathological examination showed atrophy of gastric mucosa, intestinal metaplasia or dysplasia;(2)Patients with *Helicobacter pylori* infection positive;(3)Patients with gastroesophageal reflux disease.(4)Patients with digestive system organic lesions.(5)The patient had a history of stomach or abdominal surgery.(6)Patients had taken the relevant drugs in the past 2 weeks.(7)Patients suffering from a severe illness affecting survival.(8)Pregnant or lactating women.(9)Participating in clinical trials of other drugs.(10)Long term using of sedative-hypnotics.(11)Suspected or true alcohol, drug abuse history.

### Removal, dropout, and termination criteria

2.4

#### Withdrawal of participants

2.4.1

Participants can voluntarily drop out at any time during the trial. All the participants who have filled in the informed consent form and screened for qualified entry into the trial, no matter when and why they quit, as long as they have not completed the prescribed observation period, are all cases of dropout. When participants drop out, the researcher should ask the reason, record the last time of taking medicine, complete the evaluation items that can be completed, and fill in the case report form (CRF) fall off reason table.

#### The withdrawal decided by the investigator

2.4.2

(1)Participants with serious adverse events.(2)During the experiment, the participants had some complications or special physiological changes, so they were not suitable to continue the experiment.(3)In the trial, the participants used the banned drugs specified in the trial protocol due to poor compliance.(4)According to the judgment of the doctor, there might be dangerous events. To protect the participants, they should be removed from the clinical trial and receive other treatments, and the case will be treated as invalid.

All selected cases, no matter whether they fall off or not, should record and keep the research medical record and CRF. All the report forms of the lost cases are submitted to the clinical responsible unit for summary and statistical analysis.

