#### Safety outcomes

2.10.2

The safety was evaluated by routine physical examination and laboratory examination, which will be checked before and after the intervention, to access the safety of QZWTG on patients with FD. Routine physical examination includes body temperature, respiration, blood pressure, and heart rate. Laboratory tests include blood routine, urine routine, and stool routine, stool occult blood, liver function, renal function, abdominal B ultrasound, gastroscopy, and electrocardiogram (ECG). Safety evaluation will be performed before and after the intervention. Any adverse event occurs during the study will be observed and recorded in detail.

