#### Primary and secondary outcomes

2.10.3

The primary outcomes are the change of the main symptom score contains an evaluation of postprandial fullness discomfort, early satiety, epigastric pain, epigastric burning sensation and so on. The main symptom score mainly utilized to assess the severity of symptoms and distinguish between EPS and PDS. The score will be assessed at baseline and week 2, week 4, week 6.

Owing to psychosocial factors likely play a role in FD,^[31–33]^ with greater FD symptom severity correlated with depression and somatization, this trial also includes the anxiety and depression assessment form in the assessment of secondary outcomes. The secondary outcomes mainly include TCM syndrome evaluation, the change of the Hamilton anxiety scale and the Hamilton depression scale, which will be measured at baseline and every 2 weeks during the treatment period to evaluate the changes of patients’ mental and psychological status, biochemical indicators, and changes of blood metabonomics and urine metabonomics (Table 2).

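### Section 2.4.2 removes participants in whom danger is foreseen from the trial, not only from study drug, and the article provides no observation after they leave

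*Protocol article*

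**What the plan says.** All references are to the protocol article.

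- **Section 2.4.2 (investigator withdrawal)** lists four grounds: serious adverse events, complications or special physiological changes, use of banned drugs, and the doctor's view that danger may lie ahead. The fourth reads "According to the judgment of the doctor, there might be dangerous events". The consequence follows directly: "they should be removed from the clinical trial and receive other treatments, and the case will be treated as invalid". The section then keeps the medical record and CRF of every enrolled case and adds: "All the report forms of the lost cases are submitted to the clinical responsible unit for summary and statistical analysis".
- **Section 2.4.1 (withdrawal of participants)** classes anyone who has not completed the observation period as a dropout, "no matter when and why they quit". Staff ask the reason, record the last dose, "complete the evaluation items that can be completed", and fill in the CRF table of reasons.
- **Section 2.1** sets the schedule: "After 1 week of the screening period, 4 weeks of intervention, and 2 weeks of follow-up".
- **Section 2.10.2** says "Safety evaluation will be performed before and after the intervention", and adds a general rule that adverse events arising in the study are recorded in detail.
- **Section 2.10.3**, on the main symptom score: "The score will be assessed at baseline and week 2, week 4, week 6".
- **Section 2.12** puts every randomised and dosed participant in the safety set. The FAS needs one dose and one post-treatment measurement of the main index, with LOCF for incomplete treatment courses. The per-protocol set requires, among other things, that all follow-up is completed.

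**The concern.** Stopping study drug and leaving the trial are different decisions. A doctor who fears for a participant has good reason to stop the drug and give other care. That is not in itself a reason to stop observing. Section 2.4.2 merges the two, and does so for the participants whose later course matters most for safety, which is one of the trial's stated aims.

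Two things are at stake. First, the outcome of the event that prompted removal, and any later event, may not be captured. Second, the missing symptom scores are informative, because participants leave for a reason connected with their condition or their reaction to treatment. In the FAS a carried-forward value then stands in for what could have been observed.

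A smaller matter of wording goes with this. The article does not say what treating a case as *invalid* means for the analysis.

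**Working it through.** The point is procedural. The article gives no figure to reproduce and no removal rate from which to compute an effect, so the check sets the provisions side by side.

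1. **Is the rule about the drug or about the trial?** The sentence after item (4) orders removal from the trial and other treatment. Nothing in section 2.4.2 offers stopping study drug while staying under observation.

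2. **Whom does it cover?** Certainly item (4), to which the sentence is attached. Under the section heading it arguably also covers items (1) to (3), but those items do not carry the wording themselves.

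3. **What is collected at exit?** Section 2.4.1 applies to every dropout whatever the reason and asks for the evaluations that can still be done. Read with the post-intervention safety evaluation in section 2.10.2, this should capture the triggering event and the exit tests where feasible. The gap is therefore not at exit.

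4. **What is collected after exit?** Four provisions could supply something:
   - Section 2.4.2 on records and report forms keeps and forwards what was collected. It schedules nothing new.
   - Section 2.10.2 on adverse events is a general rule. It is not limited to participants on drug, but it does not say that recording continues for someone already removed.
   - Section 3 mentions phone contact with participants at home. This is general communication and is not tied to withdrawn participants.
   - Section 2.12 applies LOCF, which imputes and does not observe.

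   None of them extends observation past removal.

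5. **Do the contacts already exist?** Yes. The schedule runs 4 + 2 = 6 weeks after treatment starts, and section 2.10.3 already places assessments at weeks 2, 4 and 6.

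6. **How does *invalid* fit section 2.12?** Three readings are open:
   - *Excluded from all analysis.* This contradicts the safety set and FAS definitions, and also the statement in section 2.4.2 that forms of lost cases go to statistical analysis.
   - *Excluded from the per-protocol set only.* This is consistent with section 2.12, since a removed participant has not completed follow-up.
   - *Ineffective, that is, a treatment failure.* This is plausible in a trial whose sample size (section 2.5) rests on an effective rate, but for an early exit it differs from carrying the last score forward.

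   The article does not settle which is meant.

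**The case against.** The strongest reply is that this is a journal article condensing a fuller protocol, and follow-up of adverse events after withdrawal is the kind of detail an article leaves out. Section 2.4.2 nowhere forbids such follow-up, and section 2.10.2 has a general rule for recording adverse events. This stands in part. A fuller protocol may hold the missing rule, and the article should not be read as proof that no follow-up took place. But the point does not rest on silence alone. The article states outright that these participants leave the trial, and a site following that sentence would end observation.

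It can also be said that exit tests, records, the count of triggering events and the safety-set denominator are all preserved, and that time after removal is off study drug. That is correct, and it limits the point to late events, event outcomes and later symptom scores.

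A reader might infer more, in three ways that the article does not support:

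- *That removed participants disappear from the analysis.* Section 2.12 keeps every dosed participant in the safety set, and in the FAS once there is one post-treatment main measurement.
- *That the rule biases the non-inferiority comparison in a known direction.* No removal rate by arm is given. The 20% allowance in section 2.5 covers missing data and loss of follow-up in total and says nothing about this reason.
- *That the share of planned weeks lost measures the harm.* Such shares hold for any early exit under the same schedule, and there is no number of removed participants to apply them to.

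**Conclusion.** The point holds in limited form. Section 2.4.2 removes participants in whom danger is foreseen from the trial and not only from study drug, and no provision in the article continues observation after that. This is certain for item (4) and arguable for items (1) to (3). The size and direction of any effect on the comparison of arms are unknown, and none is claimed. The use of *invalid* is a separate, minor ambiguity.

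This is an inexpensive improvement, not a flaw that undermines the trial. Confidence is medium. It assumes that sites follow the wording as published and that no fuller protocol overrides it. If a fuller protocol already requires follow-up after withdrawal, only the sentence in section 2.4.2 needs to be brought into line.

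**What to change.** Reword section 2.4.2 so that investigator withdrawal stops study drug only. Unless the participant withdraws consent:

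- keep the already scheduled week 2, 4 and 6 contacts, by phone if needed;
- follow each adverse event to its outcome or to week 6.

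The exit assessments are already provided for in sections 2.4.1 and 2.10.2 and need no new rule. Who stops treatment, and what other care they receive, does not change.

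State that these participants stay in the safety set, and in the FAS if its definition is met. Replace *invalid* with an explicit statement of whether it means exclusion from the per-protocol set or counting as a treatment failure. If a failure rule was meant, keep it and write it down. If per-protocol exclusion was meant, state it separately. At present these participants fall out of that set because they do not complete follow-up, and with continued contacts that may no longer be so.

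The cost is modest follow-up effort for participants off study drug, an amendment, and briefing of the 8 sites. Section 4 has recruitment starting in March 2017 and expected to end in December 2020, so an amendment would apply only to later participants.

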#### The criteria for the termination of clinical trials

2.4.3

(1)Failure of random masking;(2)The rate of unblinding was more than 20% of the sample size;(3)All follow-up evaluations were completed.

### Sample size calculation

2.5

According to previous study, the effective rate of Mosapride in the treatment of FD was around 60%.^[28–30]^ According to the ratio of test group: control group = 1:1, class I error *α* was 0.025 (1 side), class II error *β* was 0.2 (80%), and noninferior standard Δ was set as 13% to estimate the sample size, 160 participants are required for each group. Considering the possibility of missing data and loss of follow-up (20% in total), we will recruit a total of 384 participants for the 2 groups, with 192 participants in the experiment group and 192 participants in the control group.

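### The 20% loss allowance was added to the required 160 per group, not divided out, so 192 per group leave about 154 evaluable and miss the plan's own target

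*Protocol article*

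**What the plan says.** All the figures stand in section 2.5 of the Protocol article (Sample size calculation). The planning inputs are as follows:

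- Control rate: "the effective rate of Mosapride in the treatment of FD was around 60" per cent. No rate is given for the test arm.
- Allocation: "test group: control group = 1:1".
- Error rates and margin: alpha "was 0.025 (1 side), class II error" and beta "was 0.2 (80%), and noninferior standard Δ was set as 13" per cent.

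From these the article concludes that "160 participants are required for each group". It then allows for "missing data and loss of follow-up (20% in total), we will recruit a total of 384 participants", "with 192 participants in the experiment group and 192 participants in the control group".

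No other section gives a different loss rate or another basis for going from 160 to 192. Section 2.12 (Statistical analysis) says that the main efficacy indexes are analysed in both the full analysis set (FAS) and the per-protocol (PP) set.

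**The concern.** A rate of missing data and loss to follow-up is a share of the people recruited, because only they can be lost. To finish with 160 after losing 20%, the required number has to be divided by 0.8. Multiplying it by 1.2 gives a smaller number, and that is what 192 looks like. If so, the three figures in the paragraph (160 required, 20% lost, 192 recruited) cannot all hold together.

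What is at stake is whether the recruitment total delivers the evaluable number it is said to protect. This matters most for the PP set, which section 2.12 limits to participants who complete all follow-up, have at least 80% compliance, take no prohibited drugs and have no serious protocol violation. That set bears the whole loss to follow-up and may shrink further. In a non-inferiority comparison a PP result normally carries weight beside the FAS result.

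**Working it through.** **Inputs, all from section 2.5:** 160 required per group; 20% loss; 192 recruited per group (384 in total); control rate 60%; margin 13 percentage points; one-sided alpha 0.025; power 80%. The test-arm rate is not stated. Where it is needed below, 60% is assumed.

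**1. Reproduce the plan's figure.** 160 × (1 + 0.20) = 192 per group, and 2 × 192 = 384. Both match exactly, so the allowance was added to the required number.

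**2. Apply the stated loss to the stated recruitment.** 192 × (1 − 0.20) = 153.6 per group, and 384 × 0.80 = 307.2 in total. The shortfall against 160 is 6.4 per group, or 12.8 in total, and 6.4 / 160 = 4%.

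**3. Number that keeps 160.** 160 / (1 − 0.20) = 200 per group, or 400 in total. That is 16 more than planned.

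**4. Loss that 192 can absorb.** 1 − 160/192 = 16.7%.

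**5. Effect on power, taking 160 as giving 80%.** The standardised effect at 160 is then 1.960 + 0.842 = 2.802. At 153.6 it is 2.802 × √(153.6/160) = 2.745. Power is Φ(2.745 − 1.960) = Φ(0.785) = 78.4%, a loss of about 1.6 points.

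**6. Effect on power with 60% in both arms.** Power = Φ(0.13 / √(0.48/n) − 1.960), where 0.48 = 2 × 0.6 × 0.4.

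| n per group | 0.13 / √(0.48/n) | Power |
|---|---|---|
| 160 | 2.373 | 66.0% |
| 154 | 2.329 | 64.4% |

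The loss is again about 1.6 points.

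**7. What step 6 does not show.** The distance from 80% to 66% has nothing to do with the loss allowance. With 60% in both arms, the stated alpha, power and margin need (1.960 + 0.842)² × 0.48 / 0.13² = 223 per group. The figure of 160 follows from the stated alpha, power and margin only under an unstated assumption, for example a test-arm rate near 62.3%. That is a separate and larger matter. The allowance accounts only for the step from 160 to about 154.

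**The case against.** Four points can be made in the plan's favour.

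- **The base of the 20% is not spelled out.** Read as a mark-up on the required number, 160 + 32 = 192 is exact. But the article attaches the 20% to missing data and loss to follow-up, which happen among recruits. Even if a mark-up was meant, a reader would take the trial to tolerate a 20% loss when it tolerates 16.7%.
- **The FAS need not fall to 154.** Section 2.12 keeps anyone with one dose and one post-treatment measurement of the main index, and carries the last observation forward. Section 2.10.3 schedules the main symptom score from week 2, so later dropouts stay in the FAS. This stands: the shortfall is mainly one of the PP set.
- **The article does not say that the PP result decides.** It says only that both sets are analysed. This also stands. The weight given to PP here is general non-inferiority practice, not a rule of this plan.
- **The effect is small, and 66% and 64% make it look larger.** The effect is indeed under two points of power, and on the plan's own terms 80% to 78.4% is the fairer statement. The lower pair is correct for equal 60% rates, but most of its distance from 80% belongs to the base figure.

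None of these removes the inconsistency between the stated requirement, the stated loss and the stated total.

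**Conclusion.** The concern holds. Recruiting 192 per group with a 20% loss leaves about 154 per group, not the 160 that section 2.5 says are required. The shortfall is 6 to 7 per group, about 13 in total.

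The conclusion rests on one reading, that the 20% is a share of those recruited, which is the usual meaning of a loss rate. The power cost of about 1.6 points is much the same whether 160 is taken to give 80% or both arms are assumed to have a 60% rate. The error is modest and should be corrected, because the paragraph claims a protection that its own numbers do not give. Correcting it would not settle the base figure of 160, and revising the base figure would not correct it.

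**What to change.** Amend section 2.5 so that its figures agree. Either of these statements is true of the planned 384:

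- With a 20% loss, 384 recruited leave about 307 evaluable, about 154 per group.
- 384 recruited keep 160 per group as long as losses do not exceed 16.7%.

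With either one, restate power at 154 per group, give the test-arm rate on which it rests, and say that the figure refers chiefly to the PP set. If the base figure is recalculated, divide the new number by 0.8; 223 per group, for instance, would become 223 / 0.8 = 279.

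The cost is a change of wording and a slightly less favourable power figure. The correction itself requires no extra enrolment. A target of 400 would be needed only if the sponsor wished to keep both the 160 and the 20%.
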